**Online Behavioral Interventions to Increase HIV disclosure and testing**

# I. PROJECT OVERVIEW

The purpose of this project is to develop and test the efficacy of online HIV risk reduction interventions among men who have sex with men (MSM). Since 2002, Public Health Solutions (formerly Medical and Health Research Association of New York City, Inc) has worked collaboratively with researchers on using the Internet as a recruitment tool for studies of high-risk sex and drug-using behaviors in MSM and, more recently, as an intervention venue. The primary objectives of the proposed behavioral interventions are to identify and engage MSM who are sexually active, in order to increase HIV disclosure with new male sex partners, HIV testing, and condom use. The interventions will be conducted by Public Health Solutions and extend prior online intervention research.

## Protocol Summary

The study was proposed by and extends prior research of Public Health Solutions (please see Appendix A). This protocol describes an Internet-based, five-branch randomized controlled intervention, enrolling 3,000 adult MSM. The five branches include 1) a control condition receiving no intervention content, 2) a standard text-based prevention webpage (from CDC.gov site: http://www.cdc.gov/hiv/topics/msm/index.htm), 3) an 8 minute dramatic video addressing sexual risk reduction within the context of alcohol use (The Morning After), 4) a 5 minute documentary video addressing HIV disclosure, HIV testing, and condom use with the sub-context of drug use (Talking About HIV), and 5) both videos. After completing the baseline survey, eligible participants who consent to participate in the intervention will be randomly assigned to the control condition or one of the four intervention conditions. The control condition will not include the delivery of any intervention content. All participants (branches 1-5) will be asked to complete a brief post-intervention survey (to measure intentions). For those in the control condition, the intentions survey will take place immediately after consent. After the intentions survey, all participants will be automatically directed to an exit page containing links to health related web sites and hotlines. Finally, all participants will be invited via email to complete a final 60-day follow-up survey.

# II. INTRODUCTION

## Literature Review and Justification for the Study

## A resurgence in HIV transmission among men who have sex with men (MSM) is a cause for serious concern, as the number of newly diagnosed HIV infections among MSM increased 8% between 2003 and 2004.1 New HIV infections in MSM have been attributed to a number of behavioral factors including, but not limited to, safer sex fatigue, HIV treatment optimism, methamphetamine and other drug use, and easy access to sex partners through Internet hook-up sites.2 Studies have documented that MSM use the Internet for dating and sexual purposes.3-11 In fact, a recent meta-analysis of studies of online sex-seeking among MSM found that 40% of MSM used the Internet to seek sex partners.12 MSM have a considerably higher HIV prevalence rate than that of the general population, with reported sexual risk behaviors that include multiple sex partners,13, 14 unprotected anal intercourse (UAI),15-18 and alcohol and drug use, such as methamphetamines, Ecstasy (MDMA), gamma hydroxy butyrate (GHB), and ketamine.14, 19-22 The majority of research on HIV and risk behaviors among MSM has been conducted in small geographic areas or within large metropolitan cities,23 and there may be differing levels and correlates of drug use and sexual risk across geographic regions,23 contributing to or resulting in changing epidemic trends. The internet is a viable solution to reaching men across geographic regions and assessing drug use across different online populations.

The population of interest for this online intervention is MSM. Of MSM who have participated in online research, a considerable proportion of those who seek sex online may be particularly in need of Internet-based HIV prevention. They are well-educated, insured, and less likely to be exposed to offline prevention messages. 5,24-26 While online behavioral interventions have been developed and implemented successfully for treatment of certain conditions, such as depression,27 few have specifically targeted high-risk sexual behavior of MSM who meet men online. Even fewer have demonstrated the success of their methods (which have included chat room interactions around HIV and safer sex, and banner ads to promote HIV and STI testing).28, 29

A recent Public Health Solutions (formerly Medical and Health Research Association of New York City) online HIV behavioral intervention pilot successfully recruited participants online and reduced HIV risk behaviors. Men were 3 times more likely to ask their partner’s HIV status (OR=3.0, p<.001) and two times more likely to disclose their own HIV status(OR=2.2, p<.001) at 3-month follow-up compared to baseline. Additional information on pilot work and other background data can be found in Appendix A.

The proposed interventions and study design are significantly different from the pilot project, given the 5-branch, randomized control trial design. It also includes the ABC components (promotion of abstinence, faithful monogamy, and correct and consistent condom use) of HIV prevention. To the best of our knowledge, a study design evaluating the efficacy of multiple intervention approaches such as these has never been implemented or tested online with men seeking male sex partners.

**Intended/Potential Use of the Study Findings**

A recent study comparing the cost-effectiveness of HIV prevention interventions found that the two most important factors that determined cost-effectiveness were the HIV prevalence of the target population and the cost per person reached.30 In fact, one of the two most cost-effective interventions overall was showing videos in STI clinics (individual-level).30 These findings support our proposed online behavioral intervention using video vignettes in terms of cost-effectiveness and reaching high-risk MSM. If successful, this type of novel Internet-based intervention approach will be efficient, cost-effective, feasible to replicate, and especially useful in reaching men in rural areas or other hard-to-reach populations.

Specific Aims and Hypotheses

**Aim 1:** To test the feasibility of implementing an innovative national online randomized controlled, multi-branched, behavioral intervention for men who have reportedoral or anal sex with any male (new partner or not) in the past 60 days AND reported oral, anal or vaginal sex for the first time (new partner) with a male or female within the past 60 days.

**Aim 2:** a) To identify and recruit men who have sex with men met online or offline, and who, in the last 60 days, met a new sex partner; b) To enroll and randomly assign 3,000 MSM, representing diverse race/ethnicities and geography, into one control or four intervention conditions; c) To maximize retention 60-days post-intervention to complete the follow-up survey.

**Aim 3:** To evaluate the intervention conditions by comparing outcome risk measures (HIV disclosure, HIV testing, condom use, drug and/or alcohol use before sex, and depressive and/or anxiety symptomatology) at 2 time points for 5 study conditions.

**Aim 3 Primary Hypotheses:** Between baseline and 60-day follow-up there will be an increase in the following: a) HIV disclosure with new sex partners, b) HIV testing, and c) condom use in intervention branches 3, 4, and 5, compared to branches 1 and 2.

**Aim 3 Secondary Hypotheses:** Between baseline and follow-up, there will be a decrease in the following: a) drug use before sex, b) alcohol use before sex, and c) depressive and/or anxiety symptomatology in intervention branches 3, 4, and 5, compared to branches 1 and 2.

# III. PROCEDURES / METHODS

**Study Design and Location**

This Internet-based, five-branch randomized controlled intervention trial, will aim to recruit men who reside anywhere in the United States. However, the study will be managed by scientists located at Public Health Solutions in New York, NY.

**Procedures, Duration, Experimental Procedures**

We hypothesize that a brief online behavioral intervention eliciting critical thinking and attitude and behavior change will yield a reduction in sexual transmission risk, and increase HIV testing and HIV disclosure to sexual partners among MSM. By incorporating multiple approaches to online intervention content and delivery, we will test the efficacy and relative effectiveness of 4 (intervention) study conditions to improve primary outcomes of interest. The study conditions are summarized as follows:

| Branch | Description |
| --- | --- |
| 1 | control condition (i.e., shown exit page* with health links, but no intervention content) |
| 2 | standard text-based prevention webpage (http://www.cdc.gov/hiv/topics/msm/index.htm); |
| 3 | 8 minute dramatic video addressing sexual risk reduction within the context of alcohol use (*The Morning After)* |
| 4 | 5 minute documentary video addressing HIV disclosure, HIV testing, and condom use with the sub-context of drug use (*Talking About HIV*) |
| 5 | Both videos |
| *Note: all five branches will have the same list of resources available to them on the survey exit page, which will provide links to HIV testing, drug and alcohol treatment, mental health hotlines, and information about abstinence, mutual monogamy, and consistent condom use. | |

**Evaluation of Branches**

Participants in all branches will be scheduled to complete three quantitative surveys including a baseline assessment, a brief immediate post-intervention assessment (or immediate post-baseline assessment for the control group) measuring intent to change behavior during the next 60 days, and a 60-day follow-up assessment. Additionally, we will record the number of “clicks” on the resources webpage (presented after the post-intervention assessment) which represent intent to access health services and information. Our 5-branch design will allow us to directly compare, within and across branch, changes in primary and secondary outcome behaviors from baseline to 60 days follow-up. By doing so, we will be able to measure the efficacy of each of the study branches, as compared to the control branch and standard text-based prevention branch and relative to each other. The multi-branch design will allow us to directly compare the video-based interventions to the text-based prevention web-page to determine which branch elicits the most significant change in behavior.

**Theoretical Framework for Standard Text-Based Prevention Web Page**

***Branch 2:*** Internet-based information about HIV may be a useful medium for primary prevention.3 The standard text-based prevention web-page is located on the CDC.gov website (http://www.cdc.gov/hiv/topics/msm/index.htm), which contains facts about HIV among MSM, with sidebar links to prevention information, resources, publications, and other information pertaining to HIV. We will be able to time-stamp how long the participant was on the CDC web-page, based on the time between entering and exiting the web page.

**Theoretical Framework for Video Interventions**

***Branches 3-5:*** Media presentations that possess emotional qualities yield internal reflection and critical thinking,31 and there is growing evidence that dramatic or documentary narratives are more influential than written text.32 A major requirement for dramatization to be effective is that it creates an emotional response to persuade the viewer to accept the intended message.33 Film and video, in comparison with text, more often invoke “participatory responses,” essential to extended thoughts about characters, expressions of preferences about events, reflections on the broader implications of the content.34, 35 The use of film or video to create narratives, stories, or case studies, whether dramatic fiction or documentary has a powerful and enduring effect on critical thinking, attitude, and behavior change. Thus, videos are richer, more compelling, and more memorable than written text.36

The **dramatic video** (*The Morning After*, described in Appendix A) and the **documentary video** (*Talking About HIV*, described below) are based on the same theoretical framework in relation to the goal of this intervention. Both video treatments share common learning goals and the same target audience of learners. Both address the issues of sex and disclosure, condom use, and substance use (with references to HIV testing) among MSM realistically. However, they represent realism very differently. *The Morning After* is designed as a scripted drama and a fictional story with a carefully crafted plot and characters based on reality.*Talking About HIV*, excerpted from a cinema verite documentary (*Meth*), includes authentic subjective accounts, first-hand stories, and testimonials told by individuals about their own experiences.

*Talking About HIV* has been created fromdirector [name]’s (2005) documentary film, *Meth*. In *Meth*, current and past methamphetamine-using gay men share their experiences about the drug’s effect on their lives, relating to meeting sex partners, HIV disclosure, HIV infection, condom use, and the negative impact of substance use on health, family life, employment, and housing. We have developed a 5-minute documentary from the video footage, which focuses on HIV disclosure, references to HIV testing, and condom use.

The theoretical framework for this study is tailored to the objectives of promoting critical thinking and attitude and behavior change, precursors to the broader goals of increasing HIV disclosure, HIV testing, and condom use among men who have sex with men. The two video treatments in this study, though intentionally different in genre and degree of verisimilitude, are designed to challenge viewers and prompt critical thinking by portraying (and providing the vicarious experience of) dissonance, disequilibrium, and expectation failure through the instructional strategy of modeling. *The Morning After* is contextualized as a dramatic story and *Talking About HIV* is contextualized as personal accounts of stories and subjective testimonials.

Dissonance and disequilibrium both involve the discomfort felt when there is a discrepancy between what an individual already knows or believes and new information or interpretations encountered. Cognitive dissonance theories37 hold that such contradicting cognitions, and their attendant affective dimensions, are typically aroused when an individual actually needs to accommodate new ideas. When a new experience, piece of information or idea encountered does not fit well with existing knowledge and understandings, individuals experience disequilibrium.38 This frame of mind then serves as a driving force for change, creating a window of opportunity to open up to new ideas. Realistic and testimonial stories can leverage these related instructional strategies, through modeling.

One critical phase in this learning process is “expectation failure.” That is, from a cognitive science perspective, what these theories share is the belief that learning, and in particular learning critical thinking skills, is stimulated by failure. Schank39 states that “*This* is the opportunity to learn . . . Individuals realize that something was wrong with the original, existing perception of how the world works, that failure resulted from a faulty representation of something in the goal domain.” Expectation failure can be modeled, used as the basis for structuring the content in realistic stories with which viewers can identify, to stimulate critical thinking and attitude and behavior change. Thus, stories provide powerful vicarious experiences for critical thinking and attitude and behavior change.40 Both video treatments in this study attempt to set the stage for this teachable moment.

Essential to modeling, the instructional strategy associated with observational learning, is the portrayal of imperfection, flawed thinking, performance failure, problematic behavior for the viewer’s vicarious experience. As Bandura41-44 points out, we learn very little from a “perfect performance”; rather, it is from the exposure and identification of problems, and the reasoning-through-the-resolution process, that individuals are far more likely to learn. Models most effective for learning *make present* (in picture and sound) their goals and incentives; critical choices or decision points, and related strategic thinking, questioning, actions and consequences. Effective models experience trial and error; that is, effective models reveal to viewers the process of learning through failure. Models should demonstrate humanity -- frustration, self-control, effort, struggle, remorse, satisfaction, as appropriate throughout.

**Audience/Stakeholder Participation**

The primary audience for this project is men who have sex with men recruited online who have reportedoral or anal sex with any male (new partner or not) in the past 60 days AND reported oral, anal or vaginal sex for the first time (new partner) with a male or female within the past 60 days. This internet-based project inherently provides a mechanism to deliver intervention content broadly, and as a result, can directly benefit multiple governmental and community-based stakeholders committed to improving public health. We have already seeked specific guidance and feedback on intervention and evaluation content from our established community advisory board (the Internet-based Intervention Advisory Group, comprised of members of public health agencies and the online community). These individuals have also pilot-tested and commented on the baseline and follow-up surveys, as well as the text and video content.

**Risks to Respondents**

Participation is voluntary and confidential. The research involves minimal physical and social risk to participants. It is possible that participants may feel embarrassment or discomfort with the intervention videos, the surveys, or both. The only foreseeable risk would be a breach of confidentiality if participants’ email addresses were inadvertently released and linked to their survey responses.

**Protection against Risks**

Intervention and research materials will be reviewed and approved by the Institutional Review Boards (IRBs) of Public Health Solutions and the CDC prior to beginning study activities. In the unlikely event of a participant becoming distressed from answering the survey or watching the intervention videos, we will have a link to a 24-hour, toll-free mental health hotline (LifeNet: [contact]) on the exit referral page. Participants will see contact information about the local IRB and investigator to phone or email if they have any concerns or questions or experience any negative impact. Any adverse events will be reported to both Public Health Solutions and CDC IRBs.

Informed Consent: A printable online consent form will describe the study to the potential participant following a click of the study recruitment banner (please see Appendix C-1). Participants who do not wish to complete the baseline survey will be able to discontinue their participation by closing their Internet browser and will have the option of declining to answer any questions that they do not wish to answer. Those who complete the baseline survey but do not meet intervention study criteria will automatically be directed to the exit page, which contains links to HIV testing, drug and alcohol treatment, mental health hotlines, and information about abstinence, mutual monogamy, and consistent condom use (Appendix G). Those who complete the baseline survey and do meet intervention study criteria will be provided with another consent form (Appendix C-2) asking them to join the next part of the study that involves assignment to one of five branches and an additional 60-day follow-up interview. This consent also specifies that it is necessary to provide an email address to participate. The minimal risks, the confidential and voluntary nature of participation, and the fact that participants can stop their participation at any time are described in the consent form. Finally, before respondents begin the 60-day follow-up survey, they will be shown a reminder (Appendix C-3) that highlights the information presented in the second consent. See the *Informed Consent* section below for more details about these procedures.

Email addresses and data security: An email address will be the only identifying information collected; however, the email address will be encrypted and stored separately from survey data. Email addresses will be stored in an electronic file separate from survey data on a secure, firewall protected Public Health Solutions-managed server. Only the Public Health Solutions Manager of Web Development and Programming will have access to these files. If email addresses were inadvertently released, they would be un-readable. After all of the 60 day follow-up surveys have been completed, the encrypted email addresses will be destroyed. For those respondents who do not respond after 3 email follow-up attempts, we will delete the email address when their follow-up window expires. Other than email address, no other personally identifying information will be collected. No client-side persistent cookies will be used. For example, no cookies will be left on the user’s computer between the time of baseline and 60-day follow up.

Data will be stored on the Public Health Solutions, Data Link password protected server and will not be accessible by any persons who are not directly involved in the research. The server is protected by firewalls and other safeguards. Only members of the research team will have access to the data. Data will be backed up regularly and stored securely according to Public Health Solutions disaster recovery and business continuity protocols.

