**Potential Benefits**

All respondents will have the opportunity to view web links to HIV/STI, drug, alcohol, and mental health treatment at the end of both surveys and will be given an option of writing (either anonymously or by providing an email address for a response) their reactions to the survey and directing questions to the principal investigator ([name]). We successfully used this format in all of our prior online studies. Only a small proportion of participants (about 1%) have chosen to directly contact the investigators.

Benefits to society in general are anticipated through the dissemination of intervention findings (i.e., regarding high-risk sexual behavior and drug use). Results will inform local and national public health agencies about the magnitude of these problems and help them to develop outreach and prevention strategies that target Internet users, as well as the local community. Potential benefits of this type of Internet-based intervention approach include its efficiency, cost-effectiveness, and ability to be replicated.

Study Timeline

| **Date** | **Deliverables** |
| --- | --- |
| 10/06 – 05/07 | Develop Intervention Protocols |
| 10/06 – 05/07 | Develop Instruments (with consensus between CDC and Sites) |
| 10/06 – 05/07 | Develop Data Management/Sharing Plans |
| 12/06 – 06/07 | Develop Intervention Materials (e.g., videos, web pages) |
| 05/07 – 06/07 | Work with CABs/expert Advisory Groups |
| 07/07 | Submit IRB Packages to Prevention Research Branch |
| 07/07 – 09/07 | Submit IRB Packages & Obtain Approvals (Local and CDC) |
| 09/07 – 10/07 | Implement Pilot Intervention Testing |
| 10/07 – 11/07 | Fine-Tune Intervention |
| 12/07 | Submit IRB Amendments & Obtain Approvals |
| 1/08 – 5/08 | Recruit & Enroll Intervention Participants and Implement Intervention |
| 5/08 – 10/08 | Follow-up Participants (60 days post-baseline) |
| 10/08 – 12/08 | Data Cleaning & Verification |
| 01/09 – | Data Analysis |
| 01/09 – | Disseminate Findings |

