**Estimated Number of Participants**

The following estimates are based on our previous research (Appendix A). We expect that 10,522 individuals will consent to participate in the baseline behavioral assessment. Eighty percent of these individuals (8,418/10,522) will likely respond to all of the items that assess eligibility for participation in the larger intervention study. Forty-nine percent of these individuals (4,125/8,418) will likely meet the criteria for intervention inclusion, and 73% (3,000) will likely consent to participate in the intervention evaluation study.

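### The hotline offered for distress is placed on the exit page, and the protocol describes no route to it for men who stop early by closing the browser

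*Protocol*

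**What the plan says.** Protocol, Protection against Risks, names distress from answering the survey or watching the videos as an unlikely event. Its specific response is that "we will have a link to a 24-hour, toll-free mental health hotline", located "on the exit referral page". The informed-consent paragraph of the same section says that men who do not wish to complete the baseline survey "will be able to discontinue their participation by closing their Internet browser". It also says that participants can stop at any time and can decline any question.

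The protocol describes when the exit page appears:

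- Ineligible men (Protection against Risks): "Those who complete the baseline survey but do not meet intervention study criteria will automatically be directed to the exit page".
- Randomised men (Protocol Summary): "After the intentions survey, all participants will be automatically directed to an exit page containing links to health related web sites and hotlines".
- All respondents (Potential Benefits): links are offered to "mental health treatment at the end of both surveys".
- Respondents under 18 who enter their true age are skipped straight to the referral page (Exclusion of Children).
- The flow chart also appears to send men who decline the second consent to the exit page.

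Further safeguards are stated. Participants see IRB and investigator contacts for any negative impact (Protection against Risks). The first consent form carries the study email and phone number (Participant Recruitment and Enrollment Procedures). The consent forms can be printed (Informed Consent Procedures).

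**The concern.** The protocol names a risk, assigns one specific measure to it, and puts that measure at the end of the activity that could cause the distress. The stated way of leaving the baseline survey bypasses the end. A man who stops because the questions or a video upset him would then leave without the referral, although he is among those it is meant for.

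Some discomfort is foreseeable. Risks to Respondents concedes possible embarrassment or discomfort with the videos and surveys, the theoretical framework relies on dissonance and an emotional response, and the surveys include the PHQ-4 depression and anxiety items. What is at stake is participant protection and the accuracy of what the IRBs are told about it.

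**Working it through.** **Page flow.** The described routes set side by side:

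| Participant | Reaches the exit page? | Where stated |
|---|---|---|
| Completes baseline, ineligible | Yes | Protection against Risks |
| Under 18, enters true age | Yes, skipped there | Exclusion of Children |
| Declines second consent | Apparently yes | Flow chart |
| Randomised, answers intentions questions | Yes | Protocol Summary |
| Completes follow-up survey | Yes | Potential Benefits |
| Closes browser during baseline | No route described | – |
| Randomised, leaves during the activity or before finishing the intentions questions | No route described; still sent the 60-day survey link | Participant Recruitment and Enrollment Procedures |

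The rule for under-18s shows that routing a respondent to the page early can be programmed.

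**Leaving during baseline.** Estimated Number of Participants states: "Eighty percent of these individuals (8,418/10,522) will likely respond to all of the items" that assess eligibility.

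- Reproduced: 10,522 × 0.80 = 8,417.6, which rounds to the stated 8,418.
- Remainder: 10,522 − 8,418 = 2,104, and 2,104 / 10,522 = 20.0%.
- Pilot comparison (Appendix A): 3,139 − 2,777 = 362 did not complete baseline; 362 / 3,139 = 11.5%. Applied to 10,522, this gives about 1,213.

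The flow chart labels the same 80% as completion of the baseline survey. The remainder is a ceiling on men who quit, because it can include men who skipped an eligibility item and stayed.

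**Leaving after the video.** Pilot figures, Appendix A:

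- Watched the video but did not complete the post-video questions: 1,601 − 1,510 = 91; 91 / 1,601 = 5.7%.
- Men in branches 3–5: 3 × 600 = 1,800.
- 1,800 × 91 / 1,601 = 102, or roughly 100, if all 1,800 watch and the pilot rate carries over.

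Men who quit part-way through a video are not separately counted in the pilot, so no figure can be given for them. Nothing in the protocol gives the share of early leavers who are distressed.

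**The case against.** The strongest reply is that the protocol is consistent about when the exit page appears and that the hotline is not the sole protection. IRB and investigator contacts come in the very next sentence, study contacts are shown before the first survey question, and any question can be skipped. That stands, and it rules out saying that a distressed man has no protection. It does not close the gap: none of these is described as 24-hour mental-health support, and Potential Benefits reports that only about 1% of participants contacted the investigators directly.

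Three stronger readings are tempting and are not supported:

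- *The hotline appears nowhere but the exit page.* This cannot be established. The consent texts are not in the copy reviewed and the survey instrument is a separate file; either may carry the number. Only the location named in the text can be reported.
- *The safeguard misses the people it is for.* This is too broad. Distressed men who finish a stage reach the link, and nothing shows that distressed men mainly quit. The browser-closing sentence also concerns the baseline survey; extending it to the videos is a reasonable inference, not a stated instruction.
- *Nearly half of the video branches would miss the page.* In the pilot, 2,777 − 1,510 = 1,267 baseline completers (45.6%) did not finish the post-test, which applied to 1,800 would give about 820. Of those 1,267, however, 1,176 were not counted as having watched the video. Pilot men gave their email consent after the post-test, whereas here a second consent with an email address precedes randomisation. The rate does not transfer and should not be used.

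**Conclusion.** The concern holds in a limited form. The one measure aimed specifically at distress is placed on the exit page, and no described route takes a man who closes the browser early to that page. The size is at most 2,104 of 10,522 men (20%) at the baseline eligibility items, and roughly 100 of 1,800 between video and post-video questions. The second figure assumes that every man in branches 3–5 watches and leaves at the pilot rate. The number who leave because of distress is unknown and may be small, since the protocol itself calls distress unlikely. This is a minor participant-protection point. Sample size, error rate and primary analysis are unaffected.

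**What to change.** Amend Protection against Risks so that the hotline number also appears as the same plain, untracked text on every study-controlled screen in all five branches: the consent screens, the baseline and follow-up survey pages, the branch-description page (Appendix D), the video page and the intentions questions (Appendix F). Add it to the follow-up and reminder emails. In branch 2 the Appendix D page should carry it, because the CDC.gov page is not a study screen and cannot be given a footer. If the consent forms already show the number, say so in that section and add it to the survey and video screens.

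The cost is a line in the page template and a sentence in the emails, which fits the IRB amendment step scheduled for 12/07 in the Study Timeline. The downsides are slight clutter and possibly a few fewer hotline clicks on the exit page. Exit-page clicks are an additional variable compared by branch. Any loss is expected to be similar across branches, though not exactly equal, because the number of screens before the exit page differs. The definition of the click measure does not change.
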